#### Concealment mechanism {16b}

To ensure blinding, packs of inulin or placebo will be labeled as A and B by an independent person who is not involved in the trial. Both patients and investigators will be unaware of the treatment assignment. The allocation sequence will be concealed from those assigning patients to the intervention groups using opaque sealed envelopes. Randomization codes will only be unlocked after all participants have completed the trial protocol.

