#### Intervention description {11a}

Upon recruitment into the trial, patients will be randomly assigned to one of two groups. The intervention group will receive one pack of 10 g inulin (Frutafit® TEX, Sensus; DP ≥ 23) daily for 12 weeks. The control group will receive one placebo pack containing 10 g maltodextrin (Zarfructose Company; dextrose equivalent [DE] = 14) daily. Maltodextrin was chosen as the placebo because it is easily digested and has a similar appearance and taste to inulin. Inulin and placebo will be packed with the same shape, color, weight, and size. A person who is unaware of the study details will label the packs containing inulin and maltodextrin as A or B. Patients will be instructed to continue their usual diet, physical activity, and medications until the intervention is completed. They will also be given instructions on how to use their supplements. Every 4 weeks, patients will receive packs of inulin and a placebo. Additionally, weekly follow-up phone calls and clinic visits will be used to evaluate side effects and treatment compliance.

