### Assignment of interventions: allocation

#### Sequence generation {16a}

The present study will be conducted as a randomized double-blind, placebo-controlled study using a stratified randomization method. Stratified permuted block randomization will be employed to balance age (20–35 and 35–50 years) between the two groups over time. Within each of the aforementioned strata, eligible patients will be randomly assigned in a 1:1 ratio to receive either inulin or placebo with a block size of four. A block size of four will be constructed in six different arrangements (blocks) which will be created for each stratum to assign patients to the trial groups. The sequence of these blocks will be generated for each stratum using a random number generator available at randomizer.org. A person not involved in the study will randomly divide patients into two groups: intervention (inulin, *n* = 40) and control (placebo, *n* = 40).

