#### Implementation {16c}

An independent clinical research coordinator will assign patients to either the intervention or placebo group. The generation of the allocation sequence for patients will be monitored by a second researcher ([name]).

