#### Procedure for emergency unblinding if needed {17b}

The labels on the supplements will only be revealed at the final analysis stage of the study. Any unblinding that occurs during the study will be recorded and reported in the Iranian Registry of Clinical Trials, the Ethics Committee of Isfahan University of Medical Sciences, and in the final results of the study.

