### Data management {19}

One of the researchers will oversee the coding, security, and storage of data. Data will be entered electronically at the participating site, and the forms will be securely stored on file. Furthermore, they will double-check data entry and values. If any patient reports adverse events, additional information will be gathered to determine whether to exclude them from the study. According to the Medical Ethics Committee Criteria, unblinding is permissible in this situation, allowing us to specify whether the patient received inulin or a placebo.

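### Packs carry one letter per product, A or B, while unblinding is permitted during the trial, so a single code break can reveal the allocation of up to all 80 patients

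*Protocol article*

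**What the plan says.** All references are to the protocol article.

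**Labelling.** Intervention description {11a} says that a person unaware of the study details "will label the packs containing inulin and maltodextrin as A or B". Concealment mechanism {16b} repeats the scheme: "packs of inulin or placebo will be labeled as A and B by an independent person who is not involved in the trial". The letter therefore follows the product. The only participant-specific code in the article is the identification code under Confidentiality {27}, which is for storing research data.

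**When codes may be opened.** Section {16b} states that "Randomization codes will only be unlocked after all participants have completed the trial protocol", with no exception. The emergency unblinding section {17b} says "The labels on the supplements will only be revealed at the final analysis stage of the study", and then requires any unblinding during the study to be recorded and reported to the registry, to the ethics committee and in the results.

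**Permission to unblind.** Data management {19} says: "If any patient reports adverse events, additional information will be gathered to determine whether to exclude them from the study". It adds that, under the ethics committee's criteria, "unblinding is permissible in this situation, allowing us to specify whether the patient received inulin or a placebo".

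**Adverse events elsewhere.** Interim analyses {21b} describes adverse events by serious examples (death, disability, severe allergic reaction) and says the study would be discontinued if they occur.

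**The concern.** A code break is meant to reveal one patient's treatment and leave everyone else blinded. With one letter per arm it cannot. Once a team member knows what one letter means, the other letter follows by elimination, and every pack seen from then on shows its contents. Nothing in {17b} or {19} says how the other patients' blind would be kept.

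The blind matters here because the clinical outcomes depend on judgement and self-report. Headache frequency, the primary outcome, is assessed by a neurologist and by patient questionnaire. Severity is a visual analogue score, and MSQ, HIT-6 and DASS-21 are questionnaires. Staff have regular contact with the packs: under {11c} they are supplied at weeks 1, 4 and 8, and patients are asked to return them with any remaining contents at the end of each 4-week period.

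There is also a conflict of wording. Section {16b} closes the codes without exception until all participants finish, while {19} permits a team member to learn a patient's arm before then.

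**Working it through.** **Inputs from the article**
- Distinct pack labels: 2, one per product ({11a}, {16b}).
- Patients: 80, allocated 1:1 as 40 and 40 ({16a}).
- Unblinding during the trial: permitted, not required ({19}).
- Rate of unblinding: not given, so assumed values are used below.

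**Step 1. What one code break reveals.** Suppose one patient's letter is decoded.
- Patients who share that letter, including her: 40.
- Patients with the other letter, decoded by elimination: 40.
- Total: 40 + 40 = 80 of 80.
- With a unique code per participant: 1 of 80.

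The 80 is an upper bound. It applies to a person who both learns the decoded letter and can see the other patients' letters.

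**Step 2. Chance of at least one break.** If each patient independently has probability p of being unblinded, the chance of at least one break among 80 is 1 − (1 − p)^80.

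| Assumed p | Calculation | Chance of at least one break |
|---|---|---|
| 0.1% | 1 − 0.999^80 | about 8% |
| 0.5% | 1 − 0.995^80 | 33% |
| 1% | 1 − 0.99^80 | 55% |
| 2% | 1 − 0.98^80 | 80% |
| 5% | 1 − 0.95^80 | 98% |

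The result depends almost wholly on p, which the article does not supply. Sections {6b} and {22} describe the supplement as free of serious side effects at the dose used, which points to the lower rows if only serious events lead to unblinding. Step 1 does not depend on p.

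**Step 3. The sections side by side.**
- {16b} against {19}: codes closed until everyone finishes, against unblinding permitted while the trial runs. Both cannot hold as written.
- {17b} against {19}: {17b} states a general rule and then provides for recorded exceptions, so {19} can be read as one of them.
- {21b} against {19}: {21b} describes serious events that stop the study. {19} gathers information to decide whether one patient leaves, which presupposes that the study continues. The two do not clearly use the same meaning of adverse event.

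**The case against.** **Unblinding is a restricted permission.** Section {19} ties it to ethics committee criteria, and {21b} describes adverse events narrowly. If that description governs {19}, breaks would be rare, and the event that triggers one would also stop the study, leaving little of the trial to bias. This stands as a limit on frequency. It does not change what a single break reveals, and {19} reads as though the study goes on.

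**Exposure need not reach all 80.** The article does not say that the assessing neurologist handles packs, that a code break would be shared with outcome assessors, or that patients would learn it. This also stands, and it is why the figure is given as an upper bound. Nor does the article name an independent party to hold the result or say that it is kept from assessors.

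**The article condenses a fuller protocol.** Code-break mechanics may be set out there. However, the labelling scheme and the conflicting rules are positive statements in the article. That no other pack code exists is inferred from the two labelling sentences.

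**Stronger readings that the article does not support**
- A reader might infer that exclusions decided with knowledge of the arm would remove data selectively. Section {22} gives the exclusion decision to the ethics committee. Section {20c} keeps excluded patients' data in the intention-to-treat analysis, and {21b} says the same of drop-outs.
- A reader might infer from {16c}, "The generation of the allocation sequence for patients will be monitored by a second researcher", that a blinded investigator holds the list. Monitoring how a sequence is generated does not show access to the list or to the meaning of the letters, and assignment is by an independent coordinator.
- A reader might infer that side effects clustering on one letter would break the blind informally. The article gives no rates by product with which to judge this.

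**Conclusion.** The point holds as a weakness of the labelling scheme together with a conflict of wording. One permitted code break can expose up to 80 of 80 allocations, against 1 of 80 with individual codes, in a trial whose clinical outcomes are largely subjective. This rests on the letters being assigned by product, as {11a} and {16b} state, and on the person who learns the code being able to see other patients' letters.

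The article cannot settle how likely a break is. The range of 8% to 98% reflects assumed per-patient probabilities of 0.1% to 5%, and neither end should be read as a forecast. It would be too strong to say that the trial will become open-label, or that any reported adverse event must lead to unblinding. The conflict is clear between {16b} and {19}; {17b} accommodates a recorded exception.

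This should be fixed. It is not a fatal defect, because unblinding is optional, probably infrequent if confined to serious events, and does not by itself remove anyone from the analysis.

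**What to change.** 1. On packs not yet dispensed, replace A and B with a unique kit number per participant. The independent person who labels the packs holds the list linking kit numbers to product.
2. Provide single-participant sealed code breaks, so that opening one reveals one allocation, and state that the result is kept from outcome assessors.
3. Reconcile {16b}, {17b}, {19} and {21b} so that they agree on when unblinding may occur and what is meant by an adverse event for that purpose. Which events qualify is for the investigators and the ethics committee to decide.

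Suggested wording for items 1 and 2: *Each participant's packs carry a unique kit number. The list linking kit numbers to product is held by the independent labeller. A code break discloses the allocation of one participant only and is not disclosed to outcome assessors.*

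**Cost.** A small relabelling effort and a kit list. Recruitment began on August 21, 2023, so this is a change during the trial, and section {25} requires ethics committee approval for changes to study procedures. Packs already issued keep their letters, so the protection is full only for participants whose supply begins after the change. For others, a letter on an earlier pack could still be decoded if anyone who learns the code also knows that letter.

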#### Implementation {16c}

An independent clinical research coordinator will assign patients to either the intervention or placebo group. The generation of the allocation sequence for patients will be monitored by a second researcher ([name]).

### Assignment of interventions: blinding

#### People who will be blind {17a}

This study will be conducted as a double-blind study, meaning that both investigators and patients will be unaware of which group they are assigned to. Additionally, inulin and placebo will be packed with identical shape, color, weight, and size.

#### Procedure for emergency unblinding if needed {17b}

The labels on the supplements will only be revealed at the final analysis stage of the study. Any unblinding that occurs during the study will be recorded and reported in the Iranian Registry of Clinical Trials, the Ethics Committee of Isfahan University of Medical Sciences, and in the final results of the study.

### Data collection and management

#### Plans for assessment and collection of outcomes {18a}

##### Demographic variables

Demographic variables, including the type of migraine (episodic and chronic), age, anthropometric indices (height, body weight (BW), waist circumference (WC), and body mass index (BMI)), education status (university graduated and non-university graduated), marital status (single and married), migraine in first relatives, gastrointestinal problems (bloating, constipation, and diarrhea), medication (beta-blockers, anticonvulsant drugs, tricyclic antidepressants (TCA), tetracyclic antidepressant (TeCA), serotonin–norepinephrine reuptake inhibitor (SNRI)), and physical activity will be obtained from each participant at the initiation and end of the intervention using validated tools.

##### Migraine symptoms assessment

Clinical features of migraine at the initiation and end of the intervention were obtained from all participants. The migraine symptoms, such as headache frequency (number of attacks per month), severity, and duration (mean duration of headache attacks in a day per month) will be assessed by a neurologist. Participants will then be asked to complete questionnaires regarding the duration and frequency of the attacks during the intervention. The severity of pain will be assessed using a VAS ranging from 0 to 10. Participants will be instructed to score 0 if they experience no pain and 10 if they suffer from agonizing pain. The headache impact test-6 (HIT-6) scale will also be used to evaluate the degree of disability due to migraine at baseline and at the end of the trial. The HIT-6 questionnaire examines the patient’s disability as a score. The reliability and validity of this questionnaire have been established in an Iranian population [43]. Moreover, clinical symptoms of migraine, such as the migraine headache index score (MHIS), headache diary result (HDR), and migraine index (MI), will be calculated using the following formula:$$\mathrm{MI }=\mathrm{ frequency }\times \mathrm{ severity}$$$$\mathrm{HDR }=\mathrm{ frequency }\times \mathrm{ duration}$$$$\mathrm{MHIS }=\mathrm{ frequency }\times \mathrm{ duration }\times \mathrm{ severity}$$

##### Dietary intake assessment

To evaluate dietary intake, participants will be asked to maintain a 3-day food record (one weekend and two weekdays). A trained nutritionist, who will be blinded to the treatment assignment, will instruct patients on how to complete their 3-day records. The amounts of each food item and drink will then be converted to grams per day using Iranian Household Measures [44] and subsequently converted to the value of nutrients and calories using Nutritionist 4 software (First Databank Inc., Hearst Corp., San Bruno, CA, 161 USA).

##### Physical activity assessment

PA status will be assessed via the International Physical Activity Questionnaire (IPAQ), a self-administered, 7-day recall instrument whose validity and reliability have been previously approved among the Iranian population [45]. PA levels will be reported as metabolic equivalent hours per day (MET/h/day).

##### Anthropometric assessments

BW will be measured without shoes and with minimal clothing using a Seca scale with an accuracy of 100 g. Height will be measured in a standing position without shoes using a portable stadiometer to the nearest 0.5 cm. Body mass index (BMI) will be calculated using the following formula: weight (kg)/height squared (m^2^). WC will be measured by a trained dietitian at the midpoint between the lower costal margin and the iliac crest using a tape measure to the nearest 0.1 cm. Hip circumference (HC) will be measured over the widest part of the buttocks and recorded to the nearest 0.1 cm. Waist-to-hip ratio (WHR) will be calculated as WC divided by HC.

##### Assessment of quality of life (QOL)

The impact of headache on QOL will be assessed using the validated Migraine Specific QOL (MSQ) questionnaire and the HIT-6. The HIT-6 is a validated questionnaire that contains six questions with five options: “never” (score = 6), “rarely” [8], “sometimes” [10], “very often” [11], and “always” [13]. The total possible score ranges from 36 to 78. Scores between 36 and 49, 50 and 55, 56 and 59, and ≥ 60 indicate that the headache has no, moderate, substantial, and severe impact on the quality of life, respectively [46, 47]. The MSQ is a valid and reliable questionnaire that measures QOL among migraine patients over the past 4 weeks. It consists of three scales assessing three QOL domains: (1) Role Restrictive (RR), which includes seven items that assess how patients’ performance of normal activities is limited by migraine; (2) Role Preventive (RP), which consists of four items that assess how patients’ performance of normal activities is interrupted by migraines; and (3) Emotion Function (EF), which consists of three items that assess the impact of migraine on the respondent’s emotions. The item responses range from 1 to 6, with “1” representing “None of the time”, “2” representing “A little bit of time”, “3” representing “Some of the time”, “4” representing “A good bit of the time”, “5” representing “Most of the time”, and “6” representing “All of the time”. The total possible score ranges from 14 (minimal summation) to 84 (maximum summation). These scores are reverse-coded and standardized to a 0–100 scale using the following formula: (total score of each subject − 14) / 70 × 100. Higher scale scores indicate better migraine-related QOL [48].

##### Assessment of mental health status

The Depression, Anxiety, Stress Score (DASS-21) questionnaire is a self-report questionnaire that comprises 21 items, with 7 items per subscale: depression, anxiety, and stress. Patients are required to score each item on a scale ranging from 0 (did not apply to me at all), 1 (applied to me to some degree), 2 (applied to me to a considerable degree), and 3 (applied to me very much). Sum scores are computed by adding up the scores on the items per (sub) scale and multiplying them by a factor of 2. Subjects will be classified to five levels in terms of depression, where the scores of 0–4, 5–6, 7–10, 11–13, and ≥ 14 indicate the normal, mild, moderate, severe, and extremely severe depression, respectively. Also, about anxiety, the score of 0–3, 4–5, 6–7, 8–9, and ≥ 10 indicate normal, mild, moderate, severe, and extremely severe anxiety, respectively. Stress is one of the other aspects of mental status and scores of 0–7, 8–9, 10–12, 13–16, and ≥ 17 in this questionnaire indicate normal, mild, moderate, severe, and extremely severe stress, respectively [49, 50].

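### DASS-21 subscale sums are doubled but then classified with bands that fit the un-doubled sum, so severity labels shift upward

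*Protocol article*

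**What the plan says.** The section Assessment of mental health status describes a questionnaire that "comprises 21 items, with 7 items per subscale: depression, anxiety, and stress". Each item is scored from 0 to 3. The scoring rule follows: "Sum scores are computed by adding up the scores on the items per (sub) scale and multiplying them by a factor of 2".

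The same paragraph then sorts subjects into five severity levels:

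- Depression: "where the scores of 0–4, 5–6, 7–10, 11–13, and ≥ 14 indicate the normal, mild, moderate, severe, and extremely severe depression".
- Anxiety: "the score of 0–3, 4–5, 6–7, 8–9, and ≥ 10 indicate normal, mild, moderate, severe, and extremely severe anxiety".
- Stress: "scores of 0–7, 8–9, 10–12, 13–16, and ≥ 17 in this questionnaire indicate normal, mild, moderate, severe, and extremely severe stress".

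The only score the paragraph defines is the doubled one. Neither it nor any other section says that the bands apply before doubling. Mental health status is listed as a secondary outcome in the Abstract, under Outcomes and under Statistical methods.

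**The concern.** The scoring rule and the bands stand a few lines apart and do not fit each other. A doubled score runs to 42 in steps of two, while the top bands begin at 14, 10 and 17, low on that scale. A woman who gives the answer scored 1 to all seven depression items has a raw sum of 7. On the printed bands that is moderate. Doubled, it is 14, which the same bands call extremely severe.

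What is at stake is descriptive. Statistical methods says that categorical variables are reported as number and percentage. A severity table built literally from this section would place scores in categories that are too high in both arms. A reader who compares a doubled group mean with the printed bands would be misled in the same way.

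**Working it through.** **Inputs, all from Assessment of mental health status.** Seven items per subscale; item score 0 to 3; multiplier 2; lower limits of the mild, moderate, severe and extremely severe bands: depression 5/7/11/14, anxiety 4/6/8/10, stress 8/10/13/17.

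**Step 1: attainable scores.** Raw sum = 7 × (0 to 3) = 0 to 21, which is 22 values. Doubled score = 2 × raw sum = 0, 2, 4, ..., 42, again 22 values, all even.

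**Step 2: raw sums that fall in each band.**

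| Subscale | Rule | Normal | Mild | Moderate | Severe | Extremely severe |
|---|---|---|---|---|---|---|
| Depression | doubled, as written | 0–2 | 3 | 4–5 | 6 | 7–21 |
| Depression | un-doubled | 0–4 | 5–6 | 7–10 | 11–13 | 14–21 |
| Anxiety | doubled, as written | 0–1 | 2 | 3 | 4 | 5–21 |
| Anxiety | un-doubled | 0–3 | 4–5 | 6–7 | 8–9 | 10–21 |
| Stress | doubled, as written | 0–3 | 4 | 5–6 | 7–8 | 9–21 |
| Stress | un-doubled | 0–7 | 8–9 | 10–12 | 13–16 | 17–21 |

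**Step 3: share of attainable scores in the top band.**

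- Depression: 15/22 = 68% as written; 8/22 = 36% un-doubled.
- Anxiety: 17/22 = 77% as written; 12/22 = 55% un-doubled.
- Stress: 13/22 = 59% as written; 5/22 = 23% un-doubled.

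**Step 4: raw sums whose label changes.** Depression 3 to 13, which is 11 sums. Anxiety 2 to 9, which is 8 sums. Stress 4 to 16, which is 13 sums. Every change is upward. Lower and higher sums keep their label under either rule.

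**Step 5: where the top band starts.** With doubling, the lowest raw sum labelled extremely severe is 7 for depression (mean item score 7/7 = 1.00), 5 for anxiety (5/7 = 0.71) and 9 for stress (9/7 = 1.29). Un-doubled, the same sums are moderate, mild and mild.

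**Step 6: which scale the bands fit.** With doubled scores, six bands hold a single attainable value: depression 5–6 (only 6) and 11–13 (only 12); anxiety 4–5 (only 4), 6–7 (only 6) and 8–9 (only 8); stress 8–9 (only 8). On the 0 to 21 sum, every integer in every band below the top one can occur.

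**Step 7: effect on the planned tests.** Doubling multiplies both the mean difference and its standard error by 2, so t = 2d / (2 × SE) = d / SE. Ranks do not change, so neither does the Mann–Whitney test. In ANCOVA the treatment coefficient and its standard error both double. The p-values are identical, provided one convention is used at baseline and at the end.

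**The case against.** The strongest reply is that no between-group inference in the plan depends on the bands. The methods named for group comparisons are the t-test, the Mann–Whitney test and ANCOVA, and Step 7 shows that they are indifferent to doubling. Chi-square is named only for baseline comparisons, and no test of DASS-21 categories is specified. The scale plays no part in eligibility, stratification or sample size, and the labels can be rebuilt from the item responses at any time. All of this stands. It limits the point to severity labels and to the interpretation of means.

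A reader might infer that most participants would be labelled extremely severe, or that most real change would disappear inside the top band. The documents do not support either. Both need a distribution of patient scores, which the protocol does not give, and change on the continuous score is not hidden at all.

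A reader might also blame doubling for the whole of the wide top band in anxiety. That is not so, since the top band already covers 12 of 22 values without doubling.

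Finally, odd limits alone do not prove which scale the bands were built for, because integer bands have to meet without gaps. The better evidence is the compression in Steps 5 and 6. The references cited for the scale are not at hand, so the match to the un-doubled sum is a well-supported inference and not something the protocol states.

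**Conclusion.** The point holds as an internal inconsistency. Read literally, the section assigns a higher severity label to 11 (depression), 8 (anxiety) and 13 (stress) of the 22 raw sums than the same bands give un-doubled. The result rests only on the item count, the item range, the multiplier and the printed limits, and on treating the un-doubled sum as the scale for which the bands were meant. It counts score values; the number of women affected is unknown.

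It would be tempting to read this as undermining the mental health comparison between arms. It does not, because the tests on continuous scores give the same answer either way. The primary outcome is untouched. This should be fixed before analysis, but it does not threaten the trial's conclusions on treatment effect.

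**What to change.** State one convention and use it at both assessments and in the report. There are two equivalent options:

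1. Apply the printed bands to the un-doubled 0 to 21 sums, and drop the multiplication for classification.
2. Keep the doubling and double the lower limits of the mild, moderate, severe and extremely severe bands: depression 10/14/22/28, anxiety 8/12/16/20, stress 16/20/26/34.

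Enumeration confirms that both give the same label for all 22 raw sums on each subscale. Report with any mean score which convention was used. The cost is a one-sentence correction, or a new set of limits under the second option, with no new data. It is best made before the treatment codes are opened.
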